**Change in SBA in longitudinal cohorts**

Power is over 80% for a sample size of 20 in each arm for the case-community control longitudinal study (visits at 0,3,6,9,12 months) to detect a difference in SBA of 0.75. For the community cohort comparing SBA between malaria positive and negative children; 19 in each arm gives 80% power (Extended data
^
18
^).

**Changes in antibody titer by age**

 There is good power (>80%) to detect a difference of 13 antibody titer between visits for children with and without either malaria or anaemia with a sample size of 2500 (
Figure 7A–C). For malnutrition and sickle cell disease the changes in antibody titre between samples has good power (>80%) to detect a change in antibody titre of 47 and 68 respectively between visits for a sample size of 2500, which is much less sensitive than the other methods – therefore these will be exploratory endpoints (
Table 4).

**Figure 7. f7:**
[figure not shown]
**A**: Power for detecting change in SBA due to malaria infection.
**B**: Example of data from a single simulation (malaria).
**C**: Power curves for detecting impact of anaemia on mean NTS antibody level.

**Table 4. T4:** Summary of all sample size calculations carried out by risk factor and outcome.

Risk factor	Prevalence	Difference in SBA between 3 monthly samples (CFU/ml)	Difference in antibody titer	Difference in seroconversion over 3 months	Power to detect effect
*Malaria*	16%	0.25	13		>=80%
*Moderate to severe anaemia*	20%	0.225	13		>=80%
*Malnutrition*	2%	0.65	47		>=80%
*Sickle cell disease*	1%	0.9	68		>=80%
*Enteric NTS infection*	8%	0.2	15	15–20%	>=80%/ 99.97%
*Malaria RTS,S/AS01 vaccination*	60% coverage	1.5	-	-	>=80%

**Changes in serum bactericidal activity by age**

With malaria prevalence of 16%, the simulations found that 2,500 paired samples would be well-powered (power >80%) to detect changes in SBA of 0.25 CFU/ml between three-monthly samples (
Figure 8A–B,
Table 4). This change is equivalent to the gain in SBA activity naturally acquired over 2.5 months in the 9-36-month age-group, therefore lower than would be expected to be seen over a three-month period on average of natural acquisition of immunity. Simulations were run for other risk factors and protective factors including malaria vaccination (
Table 4 and
Figures 8C and 8D).

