## Methods

### Study design

**
*Prospective community cohort*
**

We will carry out a prospective cohort study with paired serology samples at baseline and 3-months taken from the same individuals. Two thousand children aged 0–5 years sampled across age-strata will be recruited, randomly sampled throughout household-censused enumeration areas. We will spread sampling evenly throughout the year in Chikwawa district, Malawi, aiming to capture peak iNTS season in the middle of the study period. These children will be evenly recruited from the vaccinated (Montfort) and non-vaccinated clusters (Chikwawa) of the EPI-MAL trial. We will select households containing children 0–5 years via a two-stage sampling technique. In the first stage enumeration areas (EA) will be selected using probability proportional to size (PPS) sampling, with stratification according to malaria prevalence. In the second stage households containing children 0–5 years will be randomly sampled from selected Enumeration Area (EA). Any child eligible in the household will be invited to participate in the study.

We will collect approximately 2500 stool samples and 4000 paired blood samples (to account for 20% loss to follow-up), measuring antibody titres (IgG) and changes in serum bactericidal activity (SBA) for the most common NTS serovars (S. Typhimurium and S. Enteritidis) and other serovars, to understand the age-stratified acquisition of immunity and how this varies with risk factor exposure. We will perform anthropometric measurements, malaria (rapid diagnostic tests [RDT] and thick blood films), haemocue and sickle RDT to assess the association with the main risk factors. Any children found to have positive malaria tests will be provided treatment by the field team. Any child with a low haemoglobin will provided treatment according to the Integrated Management of Childhood Illnesses (IMCI)/ World Health Organisation (WHO) guidelines for management of anaemia
^
17
^ and referred to hospital for follow-up. A comprehensive record of the treatments administered throughout the study will be documented for subsequent analysis. Any child diagnosed with sickle cell disease or malnutrition (based on weight-for-height z-scores or Mid-Upper Arm Circumference (MUAC)) will be referred to the local health facility for further management.

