Detailed immune and antigenic investigation of these samples will be carried out in collaboration with OptiVaNTS. An immune correlate of protection will be estimated using age-stratified acquisition of immunity and age-stratified incidence of clinical disease defined by routine blood cultures collected through MLW-Queen Elizabeth Central Hospital. Stool samples will be tested for salmonella culture and Polymerase Chain Reaction (PCR), which will enable us to model the effect of eNTS at visit 1 to induce systemic immunity at visit 2. Data will be collected on sociodemographics and indicators of water, sanitation and hygiene (WASH) using the REDCap and Open Data Kit (ODK) platforms (see
Table 1).

**Table 1. T1:** Summary of data to be collected.

Biological measure	Variable	Target n observations	Methods
Enteric Salmonella infections (usually transient & asymptomatic)	eNTS event	4000	Stool culture in selective broth, DNA extraction and qPCR for TTR gene.
Serological marker of invasive NTS infection	iNTS event	4000	ELISA for anti-S. Typhimurium and S. Enteritidis LPS IgG, conducted on 3-month paired serum samples.
Functional protective measure of serum killing	Serum killing	4000	Serum bactericidal activity high-throughput assay conducted on 3-month paired serum samples.
Rainfall and temperature	Climate	475 days	Daily measurements by Malawi Meteorological Office.
Poverty and sanitation	Poverty	4000	Validate questionnaire of household wealth and WASH (water, sanitation, and hygiene).
Current or recent malaria	MRDT	4000	Point-of-care fingerprick lateral flow antigen detection Malaria Rapid Diagnostic Test (P. falciparum HRP2 detection).
Haemoglobin	Hgb	4000	Haemoglobin (g/dl) measured by point of care fingerprick haemocue test.

We will compare the age-stratified acquisition of immunity (IgG and SBA) between children receiving the malaria vaccine (RTS,S/AS01) and un-vaccinated children matched on factors known to influence vaccine uptake. The EPI-MAL study has conducted a GPS-mapped household census, allowing us to randomly select children across the study age-strata to approach for recruitment. Selection of enumeration areas has assumed approximately 50% uptake of consent to the study, and statistical power calculations have assumed a further 10% drop out for the second visit.

Detailed schemas illustrating the rotation of field teams recruitment and sampling of stool and blood are shown in
Table 2 &
Figure 4 also see
full protocol (
*Extended data*)
^
6
^.

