**Table 2. T2:** Detailed schema of SAiNTS field illustrating teams 3-monthly rotations through sequential enumeration clusters.

		**Q1, 2021**								**Q2, 2021**								** Q3, 2021**								**Q4, 2021**								**Q1, 2022**									**Q2, 2022**			
		**V1 C1**									**V2 C1**									**V2 C2**									**V2 C3**									**V2 C4**								
											**V1 C2**									**V1 C3**									**V1 C4**																	
**RTS,S unvaccinated**	1																																													
High malaria	2																																													
prevalence	3																																													
(Chikwawa)	4																																													
N=1200	5																																													
	6																																													
	7																																													
	8																																													
	9																																													
**RTS,S vaccinated**	10																																													
Low malaria	11																																													
prevalence	12																																													
(St Montfort)	13																																													
N=1200	14																																													
	15																																													
	16																																													
	17																																													
	18																																													

Scheme showing sampling rotation through enumeration areas (EAs) (1 to 18), with four cohorts (C1 to C4) starting at 3 monthly time intervals in each of the high and low malaria transmission areas. Each EA will be visited at four time periods throughout the year, to capture variations in seasonality. A total of 2400 children will be recruited, 1200 at each site, with 30-40 children recruited over 7-12 days at each EA at each round of recruitment. Each child will have paired samples collected 3 months apart, and the next cohort of children will be recruited at the same time as the day 90 follow-up at each EA.

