**Change in SBA due to eNTS**

Statistical power is high across a range of assumptions (
Figure 6B). With a sample size of 2,500 recruited individuals, 20% loss to follow-up, a difference of 0.2 in SBA between children with salmonella PCR-positive stools compared to those with negative stools, can be detected in the three-month follow-up visit sample with 99.97% power, assuming a standard deviation of 0.4 for SBA (
Figure 6B).

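### The malaria power for SBA is stated on 2,500 pairs, but the protocol's own recruitment and loss figures give about 2,000

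*Protocol article*

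**What the plan says.** The section on changes in SBA by age opens with "With malaria prevalence of 16"% and goes on: "the simulations found that 2,500 paired samples would be well-powered (power >80%) to detect changes in SBA of 0.25 CFU/ml between three-monthly samples". Table 4 repeats 0.25 for malaria with power of at least 80%, and gives 0.225 at 20% prevalence in the row "Moderate to severe anaemia".

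The number of children, and the share expected to return, differ from place to place:

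- Study design, opening paragraph: "Two thousand children aged 0–5 years sampled across age-strata will be recruited".
- Study design, next paragraph: "approximately 2500 stool samples and 4000 paired blood samples (to account for 20% loss to follow-up"). Table 1 also gives 4,000 as the target for the serology done on paired samples.
- Study design, after Table 1: "statistical power calculations have assumed a further 10% drop out for the second visit".
- Table 2 footnote: "A total of 2400 children will be recruited, 1200 at each site".
- Change in SBA due to eNTS: "With a sample size of 2,500 recruited individuals, 20% loss to follow-up".
- Abstract: paired serology from 2,500 children.

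No SD, significance level or exact power is given for the malaria or anaemia rows. The only SD printed for SBA is 0.4, in the enteric NTS calculation.

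**The concern.** A three-month change can be computed only for a child who gives both samples. The malaria statement counts 2,500 such children, whereas the enteric NTS calculation treats 2,500 as the number before loss. If the malaria simulation really ran on 2,500 complete pairs, it used more pairs than the study plans to have.

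Malaria and anaemia are leading risk factors in specific objective 3. The protocol supports the choice of 0.25 by equating it with 2.5 months of natural gain at ages 9 to 36 months, and so placing it below the gain expected over three months. That comparison has little room: 0.25 / 2.5 × 3 = 0.30 over three months. A larger detectable difference uses up most of what remains.

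**Working it through.** **1. Can the stated figures give 2,500 pairs?** Pairs = recruited × (1 − loss).

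| Recruited | 10% loss | 20% loss |
|---|---|---|
| 2,500 | 2,250 | 2,000 |
| 2,400 | 2,160 | 1,920 |
| 2,000 | 1,800 | 1,600 |

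None gives 2,500. That would need 2,500 / 0.9 = 2,778 recruits at 10% loss, or 2,500 / 0.8 = 3,125 at 20%. The best-supported count is 2,000: it is 2,500 × 0.8, and it is 4,000 / 2 if the 4,000 bloods are individual samples taken in pairs.

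**2. Can the plan's own figures be reproduced?** With exposed fraction p, difference d, standard deviation SD and two-sided alpha 0.05 (assumed):

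power = Φ( d·√(N·p·(1−p)) / SD − 1.96 )

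- Enteric NTS: N = 2,000, p = 0.08, d = 0.2, SD = 0.4 gives 99.998%, against a printed 99.97%. That is close enough to show that the formula is of the right kind.
- Malaria: no point value can be reproduced, because only a bound is printed and the SD is missing. With SD 0.4, power at 0.25 is about 100% at every N from 1,600 to 2,500.

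**3. Where does the power at 2,500 probably lie?** Solve each Table 4 row for the SD that gives exactly 80% at N = 2,500: SD = d·√(2,500·p·(1−p)) / (1.96 + 0.8416).

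| Row | p | d | Implied SD |
|---|---|---|---|
| Malaria | 0.16 | 0.25 | 4.583 / 2.802 = 1.64 |
| Anaemia | 0.20 | 0.225 | 4.500 / 2.802 = 1.61 |
| Malnutrition | 0.02 | 0.65 | 4.550 / 2.802 = 1.62 |
| Sickle cell disease | 0.01 | 0.9 | 4.477 / 2.802 = 1.60 |

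Four rows with very different prevalences and differences give nearly the same SD. They therefore look like minimum detectable differences at one shared power level, and 80% is the only level the table names for them. This is an inference, not something the protocol states. The titre column does not show the same pattern (implied SDs from 85 to 121 across these four risk factors), so no power is inferred for titre.

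**4. Power on fewer pairs.** If power is 80% at 2,500, then at N pairs it is Φ( 2.802·√(N/2,500) − 1.96 ), and the detectable difference at 80% is 0.25·√(2,500/N).

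| Pairs | Power at 0.25 | Detectable at 80% |
|---|---|---|
| 2,500 | 80% | 0.25 |
| 2,250 | Φ(2.658 − 1.96) = 76% | 0.26 |
| 2,000 | Φ(2.506 − 1.96) = 71% | 0.28 |

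For anaemia, if its simulation also used 2,500 pairs, the detectable difference at 2,000 pairs is 0.225·√1.25 = 0.25.

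**5. How far does the anchor matter?** If power at 2,500 is 85%, it is 81% at 2,250 and 76% at 2,000. If it is 90%, these become 87% and 83%. Power stays at 80% or more with 2,000 pairs only if it is at least about 88% at 2,500; with 2,250 pairs the break-even is about 84%.

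**The case against.** The protocol claims only that power exceeds 80%. It prints no SD for malaria, the power curves cannot be seen here, and the simulation code is not at hand. If true power at 2,500 pairs is about 88% or more, the claim survives 20% loss. This stands, and it is why the loss of power can be stated only conditionally. It does not explain how 2,500 pairs arise.

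A second objection is that attrition may already be inside the simulations, since the text says the power calculations allowed for 10% drop-out. In that case the word paired in the malaria sentence is loose, and 2,500 means recruits. This is possible, but the enteric NTS calculation uses 20%, so the text would still need correcting. For anaemia and for antibody titre the objection is stronger: neither is described as resting on 2,500 pairs, and the titre statement speaks only of a sample size of 2,500.

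Third, objective 3 is worded as exploratory, and the analysis section plans coefficients with confidence intervals. That lowers the consequence of a shortfall but does not make the stated sample size right.

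Some stronger readings are tempting but not supported:

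- A reader might infer that power is really 61% to 76%. That range takes exactly 80% at 2,500 as fact. Its lower end (1,600 pairs) takes 20% off the 2,000 children, who are probably already the completers, so loss would be deducted twice.
- A reader might infer from the printed 99.97% that the enteric NTS row was run on 1,600 pairs, since these give 99.974% at two-sided 0.05. But alpha is not stated, and 2,000 pairs at alpha 0.01 give 99.976%. The gap between 99.97% and 99.998% is too small to settle which sample was used.

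**Conclusion.** The concern holds in this form: the 2,500 pairs behind the malaria SBA power conflict with every recruitment and loss figure in the protocol, which point to about 2,000 pairs. This part rests on the text alone.

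The size of the effect is conditional. It assumes about 80% power at 2,500 pairs, a two-sided 0.05 test of two means, and no allowance for clustering. On those assumptions malaria power at 0.25 falls to about 71% with 2,000 pairs (76% with 2,250), and the detectable difference rises to about 0.28. That is about 93% of the 0.30 three-month gain implied by the protocol's own benchmark, which is an average for ages 9 to 36 months only. Anaemia would move from 0.225 to about 0.25 only if its simulation also used 2,500 pairs, which the text does not say. The documents do not establish that the study lacks 80% power.

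**What to change.** State one recruitment target and one second-visit attrition rate, and use them in the abstract, the study design text, Tables 1 and 2, every sample-size subsection and Table 4. Say in each place whether a number means children recruited, children with both samples, or individual samples.

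Rerun the existing simulations on recruited × (1 − loss). Restate in the text and Table 4 the resulting power, or the difference detectable with 80% power, together with the SD and alpha used for each row. Take these figures from the rerun simulations: the 71% and 0.28 above come from a back-solved SD and should not be copied into the protocol. Then revisit the sentence that compares 0.25 with the natural three-month gain.

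The cost is one rerun of existing code and a correction to text and tables. No additional children are required, though the stated figure is likely to be less favourable.

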**Figure 8. f8:**
[figure not shown]
**A**: Power for detecting change in SBA due to malaria infection.
**B**: Example data from a single simulation (malaria).
**C**: Power for detecting change in SBA due to Anaemia.
**D**: Power for detecting change in SBA due to malaria vaccination (N=2500).

### Community engagement

A community engagement plan will be developed in collaboration with the Science Communication Department (SciCom), MLW. Sensitive issues regarding for example blood and sample collection from young children, asking personal information about poverty and concerns and fears regarding risk of COVID-19 transmission and staff working in Personal Protective Equipment will all be addressed. SAiNTS-Malawi will utilise the existing infrastructure of public engagement activities that are planned and continuously implemented by SciCom throughout the year. These include Community Advisory Group (CAG), Chiefs, District Executive committee (DEC) and other stakeholders’ meetings, Science Cafes, etc. 

### Sample storage and analysis

All laboratory process have specific SOPs which are stored in the OSF folder (
https://doi.org/10.17605/OSF.IO/FUE3T
^
6
^).

**
*Serum sample collection and processing*
**

Serum samples were collected in serum-gel vacutainers and transported daily to the main laboratory at KUHeS in Blantyre in cooler boxes with temperature loggers, maintaining a temperature of 4–8°C. Subsequently, the samples were centrifuged, aliquoted and stored at -70°C (range -65°C to -80°C).

**
*Analysis of clinical sera by ELISA*
**

Assays developed by our collaborators at GVGH will be performed as per published protocols by
Aruta
*et al.*, 2023. Briefly, antibody titers to OAg from S. Typhimurium and
*S.* Enteritidis in samples from all subjects at each time point will be analysed. Test samples, in triplicate, will be analysed at three dilutions (1:100, 1:4000, 1:160,000), and colour change compared with a standard curve made with calibrated human serum pool included on each assay plate. This pooled serum pool will be collected from high-titre adult donors in Malawi, identified from the STRATAA study (Meiring 2019) validated as the serum standard at GVGH and used across the four sub-Saharan African sites. The anti-O-Ag IgG concentration to S. Typhimurium and S. Enteriditis, in the serum standard was determined at GVGH. Anti-OAg responses will be expressed in ELISA units (EU)/ml. Test sample ELISA units are interpolated from the standard curve. Well-characterized standard OAg from
*S.* Typhimurium and
*S.* Enteritidis will be used as plate coating antigen. Positive and negative controls are created from the serum standard at set concentrations of 1.41 and 0.69 EU/ml respectively. Standard curves for each plate were assessed by a number of parameters including a minimum r-squared value, minimum (0.5) and maximum (2) optical density readings at 1 EU/ml, and maximum 20% error from expected concentration values from back-calculations (Aruta
*et al.*, 2023). BioTek™ 50TS Microplate Washer and BioTek™ 800TS Absorbance Reader will be used for the ELISAs.

**
*Analysis of clinical sera by SBA*
**

Serum Bactericidal Activity will be measured using a high-throughput fluorescent assay, which detects bacterial ATP as a readout of viability, developed by members of the VacciNTS consortium
^
19
^. The assay will be conducted in the presence of full complement repletion with 50% baby rabbit complement. Results will be available on the same day, without the need for overnight incubation or colony counting. The samples from all subjects will be analysed, in triplicate, by SBA assay using
*S.* Typhimurium and
*S.* Enteritidis wild type strains. Well-characterized cell banks of the test strains will be routinely used for the SBA. The serum standard will be tested on each plate; IC50 of the standard should be in the target range of 3x10
^3^ and 3x10
^4^. Validation checks for plates to pass quality control are outlined in [
Aruta
*et al*., 2022]. BioTek™ Synergy™ HTX Multi-Mode Microplate Reader will be used for luminescence readings.

All serological laboratory assays (ELISA and SBA) will be standardised throughout the consortium, and quality assurance between sites will be conducted, with the aim of becoming the international standard assays for use in future iNTS clinical trials, thus ensuring highly comparable dataset for modelling approaches across the consortium. Standardized sera has been validated between Malawi and GVGH to ensure reproducibility of both assays. Malawi is the African reference site for the assay. A detailed description of this SBA method has recently been published by
Aruta
*et al.,* 2022. All sample analysis will be done in Malawi for all sites, including assay transfer of the ELISA and L-SBA assays. The Ghana site will also transfer the assays to their site and will be cross-validated in Malawi.

**
*Processing and analysis of stool samples*
**

Briefly, stool samples will be collected in the field in a 30ml universal container in the field and then transported to the laboratory in Blantyre in a cold box at 4–8°C. Subsequently the sample was enriched in selenite broth and incubated overnight at 37°C before aliquoting and freezing at -70°C. Bacterial DNA extraction on the stored selenite samples will be done in batches within 14 days of collection. To avoid any age-related bias, batched analysis will be performed in the order in which the samples were collected. DNA will be extracted from pure cultures using the Omega BioTek Mag-Bind Universal Pathogen kit on the Thermo KingFisher Flex, and then sequenced using Illumina sequencing according to the manufacturer’s instructions.

The remaining selenite was cultured on XLD and incubated at 37oc overnight. Pure colonies with black centres were isolated on XLD and re-cultured on MacConkey (MAC) and Nutrient agar (NA). Oxidase test and API 20E were performed on the pure colonies from NA to identify Salmonella. Salmonella Anti-sera tests were conducted following a positive API20E identification to distinguish between O4 and O9 serovars. Pure salmonella colonies from NA were stored in a commercially purchased microbank vial. A sub-set of the batched stool samples will be tested for myeloperoxidase (MPO) using MPO stool ELISA kits (Immunodiagnostik AG, Germany, Catalogue K6630) as described in the manufacturer’s kit instructions. Stool microscopy will be carried out for the identification of parasites, ova and cysts on the day of sample collection using the Kato-Katz technique.

**
*Pan-Salmonella PCR*
**

The ttr primers and probe for the monoplex qPCR were designed and validated by the Federal Institute for Risk Assessment, Berlin, using the
*S*. enterica Typhimurium ttr locus DNA sequence (GenBank accession no. AF282268) and methods from Chirambo
*et al.* (2020)
^
15
^. For the qPCR, 200 μl of the top layer from a frozen overnight Selenite F broth stool culture was mixed with 500 μl of PBS.

An optimized PCR protocol from Chirambo
*et al.* (2020)
^
15
^ was used. The 20 μl RT-PCR master mix included 12.5 μl Platinum® Quantitative PCR Super Mix-UDG, 0.10 μl each of forward and reverse primers, 0.10 μl probe (all at 200 nM), 0.05 μl ROX dye (50 nM), and 7.15 μl nuclease-free water. This was added to 96-well plates. Test DNA, positive control DNA (D23580), and negative controls (technical extraction and UV-treated water) were added in triplicates. The qPCR run for 40 cycles on an Applied Biosystems® 7500 Real-Time PCR System, with cycling conditions of 95°C for 1 minute (initial denaturation), 95°C for 15 seconds, 60°C for 30 seconds (annealing/extension), and a final extension at 12°C. The threshold was set in the lag phase. The positive control material is DNA extracted from Salmonella enterica subsp. enterica serovar Typhimurium str. D23580. The negative control material is Nuclease Free water. An assay was deemed valid if the positive controls tested positive and both the technical extraction and assay negative controls tested negative. Test sample cycle threshold (Ct) values were assessed after baseline subtraction, with Ct values of 35 or lower considered positive.

**
*Salmonella sequencing*
**

Broth will also be plated onto agar to isolate Salmonella species and determine the range of NTS species causing eNTS episodes. Salmonella positive cultures will undergo Illumina sequencing at the Malawi-Liverpool Wellcome Research Program laboratories to provide phylogenetic analysis to understand NTS molecular epidemiology, which is important for NTS vaccine development and informing other interventions.

**
*Malaria microscopy and PCR*
**

All children will have malaria peripheral blood smears (PBS) for microscopy as well as dried blood spot (DBS) and a subset for malaria PCR testing. These will be dried in the field and transported in slide boxes at room temperature to the laboratory in Blantyre, where the films will be read by two independent, blinded trained laboratory technicians, on the day of sample collection.

